## Abstract

**Background::**

Irritable bowel syndrome (IBS) is a common functional bowel disorder. The global incidence of IBS is as high as 9% to 23%, accounting for about 50% of outpatients in gastroenterology, and the new case detection rate is 0.2% every year. IBS has become a global gastrointestinal functional disease. Although IBS is not a life-threatening disease, it seriously affects the quality of life of patients, causing huge economic and mental burden to individuals, society and families. Lipi Guben decoction (LPGBD) is an important auxiliary treatment for IBS, but lack of robust Evidence-based medicine evidence proving its efficacy. Therefore, we designed a randomized controlled trial to evaluate the efficacy and safety of LPGBD in the treatment of IBS.

**Methods::**

In this randomized controlled trial, a total of 100 eligible patients will be allocated to the blank control group or LPGBD group in a ratio of 1:1. The treatment period was 12 weeks. The primary outcome measure will be the total clinical effective rate. The Secondary outcomes will include IBS clinical symptom scores, IBS-Severity Scoring System, IBS-Quality of life, Hamilton Rating Scale for Anxiety, Hamilton Rating Scale for Depression, and Bristol Stool Form Scale. The safety outcome will include Echocardiogram, blood examination (including blood routine test, liver function test, and renal function test), urine routine test and stool routine test. The evaluation indicators and all safety results will be performed at baseline, week 4, week 8 and week 12.

**Results::**

This study will be helpful to evaluate the efficacy and safety of LPGBD in the treatment of IBS.

**Conclusion::**

LPGBD may improve the clinical efficacy of patients with IBS, which has important value in practical application

**Trial registration::**

Chictr20000039617, registration time: November 3, 2020

## Introduction

1

Irritable bowel syndrome (IBS) is a common intermittent or durative gastrointestinal functional disease characterized by abdominal pain, abdominal distension with defecation habit change, abnormal stool characteristics without organic causes.^[1]^ The global incidence of IBS is as high as 9% to 23%, accounting for about 50% of outpatients in gastroenterology, and the new case detection rate is 0.2% every year. IBS has become a growing global public health issue.^[2]^ Although IBS is not a life-threatening disease, it seriously affects the quality of life of patients, and creates a huge economic and mental burden for affected individuals, society and families. IBS have been ranked as a common cause of illness-related absenteeism, second only to the common cold. According to the study, the direct and indirect costs of each IBS patient in the United States reach US $4527 per year.^[3]^

The symptoms of IBS are complex and diverse, and the condition is complicated with an unknown etiology and pathogenesis. It is generally believed that the occurrence of IBS is the result of a combination of multiple factors, including mental and psychological disorders, visceral hypersensitivity, gastrointestinal motility disorder and intestinal infection.^[4–6]^ Clinical studies have found that diarrhoea-predominant IBS (IBS-D) is the most common type.^[6–8]^ In modern medicine, drugs that regulates intestinal movement, reduces visceral hypersensitivity, improve central emotion, and regulate intestinal flora are commonly used to relieve IBS-D symptoms.^[9–12]^ Alosetron, a selective 5-hydroxytryptamine (5-HT) receptor blocker, was once considered to be the most effective drug for IBS-D, which was approved by Food and Drug Administration (FDA). However, due to its serious side effects, it was limited to female IBS patients with severe symptoms. Although the newly developed new drugs for IBS, such as zeamak and Trevor, have certain curative effect, their clinical application is limited due to their high side effects and high price. At present, modern medicine lacks specific and effective curative drugs for the treatment of IBS. The efficacy and mechanism of traditional Chinese medicine in the treatment of IBS have attracted more and more attention.^[13–15]^

Integrated traditional Chinese medicine (TCM) and Western medicine therapy has been the most distinctive methods in the treatment of IBS in China.^[16,17]^ Integrated TCM and Western medicine therapy for IBS patients could reduce symptoms, anxiety, depression, and improve quality of life.^[18–23]^ However, due to the small sample size and unscientific research methods, the conclusions are limited. Therefore, we conducted a randomized controlled trial (RCT) to evaluate the efficacy of safety of Lipi Guben decoction (LPGBD) in the treatment of IBS.

## Methods

2

### Trial design and registration

2.1

This is a RCT. Participants will be recruited from the outpatient clinics of the First Affiliated Hospital of Guizhou University of TCM. The Figure 1 shows the study design in the flowchart, and the Figure 2 illustrates the time schedule of enrolment, interventions, assessments, and visits of participants. The reporting of this trial is conducted according to the Standard Protocol Items: Recommendations for Intervention Trials (SPIRIT) guidelines (Additional file 1).

**Figure 1 F1:**
[figure not shown]
Study flow diagram.

**Figure 2 F2:**
[figure not shown]
Study design schedule.

This protocol has been registered in the Chinese Clinical Trial Registry on November 3,2020, http://www.chictr.org.cn/edit.aspx?pid=63618&htm=4. And the registration number is ChiCTR2000039617.

### Patient population and eligibility criteria

2.2

**Inclusion criteria:**

(1)Patients meet the the Rome III diagnostic criteria for IBS-D;(2)Those who agree to participate in this study and are willing to sign informed consent.(3)The age ranged from 18 to 65 years old.

**Exclusion criteria:**

(1)Under 18 years old or over 65 years old;(2)A woman who is pregnant or is preparing for pregnancy, and lactating.(3)Intestinal organic diseases, such as inflammatory bowel disease, intestinal tuberculosis, colon polyps;(4)Patients with severe cardiovascular and cerebrovascular diseases, liver, kidney, hematopoietic system diseases and tumors;(5)There were records of digestive tract operation;(6)Patients with severe primary diseases and mental disorders;(7)Patients with allergic history or drug and food allergy during the test period;(8)Those who do not sign informed consent(9)Those who do not meet the inclusion criteria, fail to use drugs according to the regulations, cannot judge the curative effect or incomplete data, which affects the evaluation of efficacy or safety.(10)The researchers consider it inappropriate to conduct this clinical trial.

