### Randomization

2.4

Patients who met the inclusion criteria will be randomly assigned to blank control group and LPGBD group in the ratio of 1:1. Measures to Reduce the Risk of Bias Concealed randomization prevents selection bias. The random allocation sequence listing was generated by a statistician who will not participate in the clinical study using SAS v9.4 (SAS Institute, Cary, NC).5-10 minutes before treatment, the doctor will inform the patient about the randomization procedure, telephone number and name; then, the doctor will be informed of the random number of patients and the treatment group. The randomization information will be concealed until the end of the trial.

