### Blinding

2.5

Due to the nature of TCM, doctors and patients will know the grouping information. However, principal investigator, statisticians, and outcome evaluators will be blinded to group allocation.

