### Patient safety

2.8

Potential adverse events associated TCM include rash, skin allergy and liver and kidney function damage. Clinicians record the occurrence of any adverse events and the intervention will be stopped immediately. The independent safety supervision committee composed of 3 experts from different fields in the First Affiliated Hospital of Guizhou University of TCM has the right to terminate the study.

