## Statistical analysis

9

The clinical results will be analyzed by SPSS 22.0 statistical software (IBM SPSS statistics, IBM Corp, Somers, NY). In this study, the intention-to-treat analysis and per-protocol analysis will be conducted. Primary outcomes will be based on the per-protocol analysis, with the intention-to-treat analysis analysis conducted to assess robustness of the results. The measurement data will be expressed as mean ± standard deviation, and the counting data will be expressed as percentage, will be tested by a t test and chi-square test respectively. All statistical tests will be 2-sided and *P* values less than .05 will be considered to be statistically significant.

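### Exclusion criterion (9) lists events that can be known only after randomisation, which conflicts with the intention-to-treat check in section 9

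*Protocol article*

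**What the plan says.** In section 2.2 of the Protocol article, item (9) of the exclusion criteria begins with failure to meet the inclusion criteria, which is a baseline matter. It then adds patients who "fail to use drugs according to the regulations, cannot judge the curative effect or incomplete data, which affects the evaluation of efficacy or safety". Item (7) reads "Patients with allergic history or drug and food allergy during the test period".

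Section 2.4 describes entry to randomisation: "Patients who met the inclusion criteria will be randomly assigned to blank control group and LPGBD group in the ratio of 1:1". Section 9 states that "the intention-to-treat analysis and per-protocol analysis will be conducted" and ranks the two: "Primary outcomes will be based on the per-protocol analysis, with the intention-to-treat analysis analysis conducted to assess robustness of the results".

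On harms, section 2.8 says "Potential adverse events associated TCM include rash, skin allergy and liver and kidney function damage" and "Clinicians record the occurrence of any adverse events and the intervention will be stopped immediately". Section 4.3 requires the details of any adverse event to be entered in the case record form. On blinding, section 2.5 says "Due to the nature of TCM, doctors and patients will know the grouping information".

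**The concern.** An exclusion criterion decides who belongs to the trial. If it depends on what happens after allocation, patients can be declared ineligible because of how they behaved or fared on treatment, and the comparison loses the protection of randomisation.

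This matters more than usual here because the primary analysis is per-protocol. The intention-to-treat analysis is the only stated safeguard on it, and that safeguard works only if non-adherent and incompletely observed patients are in the set. There is also reason to doubt that losses would be balanced. Patients and treating doctors know the allocation, only the LPGBD arm takes a twice-daily decoction on top of conventional treatment (sections 3.1 and 3.2), and the intervention is stopped when an adverse event occurs. A patient whose treatment is stopped could then meet item (9).

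**Working it through.** **1. Timing of each item**

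| Item | When it can be known | Place in a trial plan |
|---|---|---|
| (9), inclusion criteria not met | Before randomisation | Eligibility |
| (9), drugs not used as specified | After treatment starts | Per-protocol definition |
| (9), effect cannot be judged | At outcome assessment (week 12, section 4.1) | Per-protocol definition or missing-data handling |
| (9), incomplete data | During or after follow-up | Per-protocol definition or missing-data handling |
| (7), allergic history | Before randomisation | Eligibility |
| (7), allergy in the test period | Unclear: around enrolment, or on trial | Eligibility if known beforehand; adverse event if on trial |

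**2. Section 2.2 against section 9**

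A per-protocol set normally omits non-adherent and non-evaluable patients. If item (9) has already removed the same patients from the trial, the intention-to-treat set loses them too. The two sets then nearly match, and comparing them tests little.

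**3. The plan's own figures**

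The point has no stated figure of its own. Section 2.3 supplies two of the inputs used below: 73% response under control and 20% loss. The 41 per arm in that section reproduces from its inputs (73% against 93%, two-sided alpha 0.25, power 90%):

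- n = [1.150 × √(2 × 0.83 × 0.17) + 1.282 × √(0.73 × 0.27 + 0.93 × 0.07)]² / 0.20² = 40.2, rounded up to 41.
- For the total, 82 × 1.2 = 98.4 and 82 / 0.8 = 102.5. The stated 100 lies between them.

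Nothing in the present point turns on these figures.

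**4. Possible size of the selection effect (illustration)**

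Assumptions not in the documents: true response is 73% in both arms, 50 are randomised per arm, and exclusions occur in the LPGBD arm only. With share excluded d and response r among the excluded:

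observed LPGBD rate = (0.73 − d × r) / (1 − d)

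Example: d = 0.20, r = 0 gives 0.73 / 0.80 = 0.9125. The last column is the normal-approximation probability of rejecting at two-sided 0.05 (the level in section 9), with 50 control patients against 50 × (1 − d) LPGBD patients.

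| d | r | Observed LPGBD rate | Inflation (points) | Rejection probability |
|---|---|---|---|---|
| 20% | 0% | 91.2% | 18.2 | about 60% |
| 20% | 25% | 85.0% | 12.0 | about 27% |
| 20% | 50% | 78.7% | 5.7 | about 9% |
| 20% | 73% | 73.0% | 0 | 5% |
| 10% | 0% | 81.1% | 8.1 | about 15% |
| 10% | 25% | 78.3% | 5.3 | about 9% |
| 10% | 50% | 75.6% | 2.6 | about 6% |
| 10% | 73% | 73.0% | 0 | 5% |

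The planned difference is 93 − 73 = 20 points.

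**5. What a real intention-to-treat check could show**

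Suppose the retained patients respond at 93% and 73%, and everyone excluded is counted as a non-responder (one possible convention, assumed here).

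- 20% excluded in each arm: 0.93 × 0.80 − 0.73 × 0.80 = 0.744 − 0.584 = 16.0 points.
- 20% LPGBD, 10% control: 0.744 − 0.657 = 8.7 points.
- 20% LPGBD, none in control: 0.744 − 0.730 = 1.4 points.

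This spread can be seen only if the patients remain in the set.

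**The case against.** The strongest reply is that item (9) is a per-protocol rule printed in the wrong list. Section 9 names two distinct analyses, which would be pointless if the sets were the same. Section 2.3 counts the 20% lost within the 100 recruited, and section 2.7 records reasons for withdrawal, so such patients are treated as participants. Definitions of analysis sets may properly sit in a statistical analysis plan that is not shown. Much of this stands: the authors may well have meant item (9) that way, and the missing definitions are not the complaint. It does not remove the conflict, because the printed text still makes these patients ineligible and nothing in the article says they are kept.

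A reader might infer that the intention-to-treat analysis is already a completers analysis. The documents do not support that as fact, since no section says these patients leave that set.

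A reader might also infer that allergic reactions to LPGBD would vanish from the safety results. That is not supported either. Sections 2.8 and 4.3 require adverse events to be recorded, and no section provides for discarding them. Item (7) mixes a valid baseline criterion with loosely worded text that may refer to enrolment. Section 2.8 attributes skin allergy to traditional Chinese medicine in general and gives no rate, so any reaction frequency would be guesswork.

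Finally, the 20% in section 2.3 is loss to follow-up. The article neither equates it with item (9) nor caps item (9) by it.

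**Conclusion.** The point holds for item (9). It sets exclusions that can be known only after randomisation and, applied as written, conflicts with the intention-to-treat robustness check in section 9. This is a rule stated wrongly, not a detail left out.

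The illustrated inflation is 0 to about 18 points. It rests on three assumptions: equal true response of 73%, 20% excluded from the LPGBD arm alone, and response among the excluded between 73% and 0%. The upper end is an extreme case. There is no bias if exclusion is unrelated to arm and outcome.

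Item (7) is a lesser, conditional matter. If its wording means on-trial reactions, it overlaps with the skin allergy that section 2.8 expects as an adverse event, and the passages must be reconciled.

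**What to change.** - Limit the exclusion criteria in section 2.2 to facts known before randomisation.
- Delete non-adherence, unjudgeable effect and incomplete data from item (9), and place them in the definition of the per-protocol set.
- Clarify that the allergy wording in item (7) refers to allergy known before randomisation.
- State in section 9 that all randomised patients stay in the intention-to-treat set and all treated patients in the safety analysis.

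The cost is a wording amendment and slightly more analysis work to handle missing outcomes in the intention-to-treat set. No new patients or procedures are needed.

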### Sample size

2.3

The sample size was calculated based on the total clinical effective rate at 12 weeks. According to the previous literature,^[24]^ we hypothesized that the total clinical effective rate of the blank control group and LPGBD group at 12 weeks will be 73% and 93%, respectively. Set a=0.25 (2-sided) and b = 0.10. We use PASS 15 software (PASS 15.0.5 NCSs, LLC, USA) to calculate the size of the blank control group and LPGBD group N1 = N2 = 41. Assuming that 20% of patients may be lost during follow-up, a total of 100 patients will be recruited.

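### The sample size was calculated at a two-sided alpha of 0.25 but the trial tests at 0.05, so the stated 90% power is really about 67-71%

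*Protocol article*

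**What the plan says.** Section 2.3 (Sample size) bases the calculation on the primary endpoint. It assumes that "the total clinical effective rate of the blank control group and LPGBD group at 12 weeks will be 73% and 93%, respectively". The error rates are given as "Set a=0.25 (2-sided) and b = 0.10", that is, 90% power at a two-sided level of 0.25. The result is reported as "calculate the size of the blank control group and LPGBD group N1 = N2 = 41". The section then allows for dropout: "Assuming that 20% of patients may be lost during follow-up, a total of 100 patients will be recruited". Allocation is 1:1 (section 2.4), so 50 patients are recruited per arm.

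Section 9 (Statistical analysis) sets the level for the analysis: "All statistical tests will be 2-sided and *P* values less than .05 will be considered to be statistically significant". It names the chi-square test for count data and states that "Primary outcomes will be based on the per-protocol analysis", with intention-to-treat as a check on robustness.

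The article gives no reason for sizing at one level and testing at another.

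**The concern.** The sample size is justified at a significance level five times as lenient as the one that will decide the result. A lenient level makes a small trial look well powered. Tested at 0.05, the same number of patients has a much smaller chance of showing the assumed effect.

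What is at stake is the justification for the trial's size on its primary endpoint. If LPGBD does raise the effective rate from 73% to 93%, the sponsor believes the trial will miss this one time in ten, when the true figure is nearer three in ten. Anyone who takes the 90% at face value would give a non-significant result more weight as evidence against benefit than the design supports. The Introduction also faults earlier studies for their small samples, and a trial of this size at 0.05 is exposed to the same criticism.

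**Working it through.** **Inputs.** Rates p1 = 0.73 and p2 = 0.93, beta = 0.10, sizing alpha = 0.25 two-sided, 41 per arm, 20% loss and 100 recruited (all section 2.3). Analysis alpha = 0.05 two-sided, chi-square test, per-protocol set primary (section 9). Ratio 1:1 (section 2.4).

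**Formula.** For the pooled two-proportion Z test, with d = p2 − p1 and p̄ the mean of the two rates:

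n per arm = [ z(1−α/2)·√(2p̄(1−p̄)) + z(1−β)·√(p1(1−p1) + p2(1−p2)) ]² / d²

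Here d = 0.20 and p̄ = 0.83. The two roots are √0.2822 = 0.5312 and √0.2622 = 0.5121, and z(0.90) = 1.2816.

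**Step 1: reproduce the plan's figure.** At alpha 0.25 two-sided, z = 1.1503:

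n = (1.1503 × 0.5312 + 1.2816 × 0.5121)² / 0.04 = (0.6111 + 0.6562)² / 0.04 = 40.15, so **41 per arm**. This matches section 2.3.

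**Step 2: the same inputs at the analysis level.**

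| Two-sided alpha | Power | n before rounding | n per arm |
|---|---|---|---|
| 0.25 | 90% | 40.15 | 41 |
| 0.05 | 90% | 72.03 | 73 |
| 0.05 | 80% | 54.18 | 55 |
| 0.025 | 90% | 85.28 | 86 |

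Had 0.25 been a slip of the pen for 0.05 or 0.025, the reported size would have been 73 or 86.

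**Step 3: power at two-sided 0.05 for the planned numbers.** Solving the formula for power:

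power = Φ( [ d√n − 1.9600 × 0.5312 ] / 0.5121 )

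- n = 41: (1.2806 − 1.0412) / 0.5121 = 0.468, so 68.0%.
- n = 40, which is 50 recruited less 20%: (1.2649 − 1.0412) / 0.5121 = 0.437, so 66.9%.
- n = 50, with nobody lost: (1.4142 − 1.0412) / 0.5121 = 0.728, so 76.7%.

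Two other methods for the same quantity:

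| Analysed per arm | Pooled normal | Unpooled normal | Exact, uncorrected chi-square |
|---|---|---|---|
| 40 | 66.9% | 69.5% | 70.2% |
| 41 | 68.0% | 70.6% | 71.4% |
| 50 | 76.7% | 78.9% | 80.3% |

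The exact column sums the binomial probabilities of all tables with P < 0.05. A more conservative test lowers power further: Fisher's exact test gives 59.6% (n = 40) and 61.2% (n = 41), and the Yates-corrected chi-square gives 54.7% and 56.4%.

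**Step 4: detectable effect.** With 40 evaluable per arm and 73% in the control group, the pooled formula reaches 80% power at a true LPGBD rate of about 95.5% (80.1%). The exact chi-square calculation gives 79.2% power at 94.5% and 82.1% at 95%, so it reaches 80% a little above 94.5%.

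**Step 5: size for 90% power at 0.05, with the stated loss.** 73 / 0.80 = 91.25, so 92 per arm and 184 in total, against 100 planned.

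**The case against.** Nothing in the article reconciles the two levels, and condensation into a journal article does not explain them, because both are printed. A separate analysis plan could not help either: it cannot make 41 per arm give 90% power at 0.05. The serious objections concern how far the claim reaches.

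- **Whether 0.25 really was the value used.** Section 2.3 does not name the procedure run in the software. With the stated inputs, the pooled formula gives 41, but the unpooled and arcsine versions give 39 and a continuity correction gives 50. Some unstated inputs also give 41, for example one-sided 0.05 with 80% power, unpooled. This stands as a caution. Those inputs, however, contradict both the two-sided test and the beta of 0.10 in section 2.3, and under them the 90% would still be wrong. The shortfall at 0.05 does not depend on how 41 came about.
- **The analysis set.** An intention-to-treat analysis of all 50 per arm at the same rates would have 76.7% to 80.3% power. This is true and should be said. But the primary analysis is per-protocol and the plan itself expects 20% loss, so 40 per arm is the relevant number. Even 50 per arm falls short of 90%.
- **Mixed methods.** The 95.5% detectable rate is a pooled-formula figure and is somewhat lower by exact calculation. The Fisher and Yates figures apply only if one of those tests is used, since section 9 says just chi-square. Both points are fair, and any figure written into the protocol should name its method.
- **How a null result would be read.** The article does not say, so that consequence is a risk and not a stated intention. The loss of power does not depend on it.

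**Conclusion.** The point holds and must be corrected. For 73% against 93% at two-sided 0.05, the design has 66.9% to 71.4% power with 40 to 41 evaluable patients per arm, not 90%. The type II error is about 0.29 to 0.33, roughly three times the stated 0.10.

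This rests on the plan's own rates, 1:1 allocation, 20% loss and the per-protocol set as primary, with the uncorrected chi-square test or its normal approximation. Confidence is high: the plan's 41 is reproduced exactly from its stated inputs, and no method or analysis set examined here brings power at 0.05 up to 90%.

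**What to change.** In section 2.3:

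1. State the significance level as 0.05 two-sided, in line with section 9.
2. Change the beta of 0.10 and the sentence deriving 41 per arm at the same time. Changing alpha alone would leave a false statement, since 0.05 with 90% power gives 73. As recruitment was already under way (section 11), record that 41 was obtained at an alpha of 0.25.
3. State the power that 100 recruited patients deliver: with 40 evaluable per arm and 73% against 93%, about 67% (pooled normal approximation) or 70% (exact, uncorrected chi-square).
4. State the effect detectable with 80% power at that size: 73% against about 95.5% by the pooled formula, naming the method.

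If the sponsor wishes to keep 90% power, the matching figures are 73 evaluable per arm and 184 recruited with 20% loss. That is a choice for the sponsor and is not needed for the correction.

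The cost is a change of protocol wording. Conduct and analysis stay as they are, and the price is a less favourable stated power.

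### On the plan's own figures, 100 recruited less 20% leaves 40 evaluable per arm, one short of the stated 41; minor alone, but the evaluable number and its power should be restated

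*Protocol article*

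**What the plan says.** All the planning figures are in the Sample size section (2.3) of the protocol article. It assumes that "the total clinical effective rate of the blank control group and LPGBD group at 12 weeks will be 73% and 93%, respectively", sets the error rates with "Set a=0.25 (2-sided) and b = 0.10", and reports that the software was used to "calculate the size of the blank control group and LPGBD group N1 = N2 = 41". It then moves from the evaluable number to the recruited number in one sentence: "Assuming that 20% of patients may be lost during follow-up, a total of 100 patients will be recruited". No inflation formula is given.

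Two other sections matter here. Under Randomization (2.4), patients are "randomly assigned to blank control group and LPGBD group in the ratio of 1:1", so 100 recruits means 50 per arm. Under Statistical analysis (9), "Primary outcomes will be based on the per-protocol analysis", with intention-to-treat as the robustness check, and "All statistical tests will be 2-sided and *P* values less than .05 will be considered to be statistically significant".

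**The concern.** A dropout allowance exists so that the required number is still available after the assumed losses. Here the required number, the assumed loss and the recruitment total stand in the same paragraph and do not agree. If the assumed loss occurs, the trial ends with fewer evaluable patients than the paragraph says it needs.

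This reaches the main result because the primary analysis is per-protocol, so patients lost to follow-up leave its denominator. The allowance also has no slack. The Discussion (10) itself expects a high dropout rate because of the long observation period, and the 20% is described as loss during follow-up, so it does not visibly cover patients dropped from the per-protocol set for non-adherence.

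At stake are the internal consistency of the sample size statement and the power figure a reader takes from it.

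**Working it through.** **Inputs.** Effective rates p1 = 0.73 and p2 = 0.93, alpha 0.25 two-sided, beta 0.10, 41 per arm, 20% loss and 100 recruited (all Sample size); 1:1 allocation (Randomization); test level 0.05 two-sided and per-protocol primary (Statistical analysis).

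**1. Reproduce the 41.** Normal-approximation formula for two proportions, pooled variance under the null, no continuity correction:

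n = [z(1−α/2)·√(2·p̄·q̄) + z(1−β)·√(p1·q1 + p2·q2)]² / (p2 − p1)²

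- p̄ = 0.83, so √(2 × 0.83 × 0.17) = √0.2822 = 0.531
- √(0.73 × 0.27 + 0.93 × 0.07) = √0.2622 = 0.512
- z(0.875) = 1.150 and z(0.90) = 1.282
- n = (1.150 × 0.531 + 1.282 × 0.512)² / 0.04 ≈ 40.2, rounded up to 41

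The plan's figure is reproduced exactly at alpha 0.25. At the same alpha and power, the unpooled variant gives 39 and the continuity-corrected one 50.

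**2. Apply the stated loss to the stated recruitment.**

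- Evaluable in total: 100 × (1 − 0.20) = 80, against 2 × 41 = 82 required
- Evaluable per arm: 50 × 0.80 = 40, against 41
- Largest loss that 100 recruits can absorb: 1 − 82/100 = 18%

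**3. Where 100 may have come from.** Dividing gives 41/0.80 = 51.25 per arm (82/0.80 = 102.5 in total). Multiplying gives 41 × 1.2 = 49.2, which rounds up to 50 per arm and 100 in total. The stated total fits the second form, but the protocol does not say which was used.

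**4. Power at the resulting sizes.** Power = Φ{[(p2 − p1)·√n − z(1−α/2)·0.531] / 0.512}:

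| Evaluable per arm | Alpha 0.25, two-sided | Alpha 0.05, two-sided |
|---|---|---|
| 40 | 89.9% | 66.9% |
| 41 | 90.5% | 68.0% |
| 50 (no loss) | 94.2% | 76.7% |

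Moving from 41 to 40 per arm costs about half a point of power at alpha 0.25 and about one point at 0.05. Moving from alpha 0.25 to 0.05 with 40 per arm costs 89.9 − 66.9 = 23 points. At two-sided 0.05 with 90% power, the formula in step 1 gives 73 per arm.

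**The case against.** The strongest reply is that nothing turns on this. The 20% is a planning guess, 100 is a round number, and power with 40 per arm is 0.1 point below the 90% target on the plan's own alpha. If every randomised patient were counted under intention-to-treat, 50 per arm would be available. The judgement on size stands: this is not a material sample size error by itself. It does not remove the inconsistency, because the primary analysis is per-protocol and the three figures in the paragraph still do not fit together.

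A second reply is that the alpha conflict overtakes the point: once the level is settled, both 41 and 100 will be revised. That is also largely right, and it is why the correction belongs in the same revision. It does not make the point empty, since the revised number will need a loss allowance too.

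A reader might infer more than the document supports in three ways:

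- **That the authors multiplied by 1.2.** The total is consistent with this, but no formula is stated. Multiplying the overall 82 gives 98.4, and 100 could equally be 102.5 taken to a convenient figure.
- **That recruitment should rise to 104 (52 per arm).** This keeps a 41 that reproduces at alpha 0.25. With 41 evaluable per arm, power at two-sided 0.05 would still be about 68%, so the sample size would look corrected without being so.
- **That the dropout slip leaves the trial underpowered.** It does not. The low power at 0.05 comes almost entirely from the difference between the two alpha levels.

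**Conclusion.** The point holds as a minor inconsistency. Under the stated 20% loss, 100 recruits give 40 evaluable per arm, not the 41 required, and cover an 18% loss. Taken alone, this lowers power from 90.5% to 89.9% at the stated alpha of 0.25. At the level at which the trial will actually be tested, two-sided 0.05, 40 per arm gives about 67%; that figure reflects the alpha conflict and not the dropout allowance.

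The count of 40 rests only on the protocol's own numbers, with the loss read as a share of those recruited and spread equally over the arms. The power figures also assume the planned rates of 73% and 93% and the pooled normal approximation that reproduces the 41. How the 100 was derived remains unknown.

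**What to change.** In the Sample size section, state that recruiting 100 patients gives 40 evaluable per arm after 20% loss, and give the power for 40 per arm at the two-sided 0.05 level of the Statistical analysis section: about 67% for 73% versus 93%. When the two alpha levels are reconciled, derive any new recruitment figure as n/(1 − 0.20) and state that formula.

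The restatement is a short text change and needs no extra patients. Its only cost is that the protocol would show a power well below the 90% it now implies.
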